While designing the impact evaluation of the UP pilot, the following contextual variations in the scale of direct beneficiaries were considered. The program engaged ANMs (>400 in UP vs >9000 in Telangana and >15,000 in AP), MOs (>100 in UP vs >1000 in Telangana and >1800 in AP), and specialists (>10 in UP vs >400 in Telangana and >500 in AP). Indirect beneficiaries also varied substantially, with approximately 60,000 pregnancies per year in UP compared with 700,000 in Telangana and 900,000 in AP, translating to roughly 18,000 HRPs per year in UP versus 200,000 in Telangana and 300,000 in AP. Training timelines also differed, while training all ANMs on 6 phase-1 protocols required approximately 1 year in Telangana and 9 months in AP, >400 ANMs in UP were trained in just a few days. Moreover, digital interventions were introduced within 2-3 months of program initiation in UP, compared with more than 3 years in Telangana and 1 year in AP, as these digital interventions were still evolving when implementation began in Telangana.

Thus, considering UP’s comparative advantage over Telangana and AP, sufficient number of direct and indirect beneficiaries, the rapid introduction of all interventions in quick succession, and additional scope for keeping a control arm, the UP impact evaluation design is expected to provide generalizable evidence on the program’s impact, even with its shorter duration (18 months) and smaller scale (2 intervention districts and 3 HRP protocols). In UP, the impact evaluation will be confined to the following 3 HRP conditions: anemia (moderate and severe), PIH, and APH.

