## Methods

### Study Design

The study adopts a “matched, before-after quasi-experimental design with a control (usual care) arm,” as a randomized control study design is not feasible for this kind of system and community-based implementation study. Both qualitative and quantitative data will be collected at the system and community levels, respectively, during baseline (prior to implementation of interventions) and end line (after 18 months of interventions)*,* in the intervention and control arms. The program’s effectiveness at the system level will be evaluated by assessing the capacity of ANMs and MOs to diagnose and manage the 3 HRPs and at the community level by measuring the proportion of RDW with any of the HRP conditions, whose HRP problem got resolved prior to delivery and who were satisfied with the care they have received for the HRP condition*.* Effectiveness of the program through quantitative indicators will be analyzed using the difference-in-difference (DiD) technique.

However, keeping in view the quasi-experimental design of this study, to control for potential baseline differences between intervention and control arms due to nonrandom allocation, we will lock the analysis plan by prespecifying primary outcomes and covariates of the quantitative data. Prior to advanced analyses, we will implement near-matching of intervention and control data on key covariates, such as age, parity, caste, and literacy. In addition, during the main analysis stage, we will apply DiD models with covariate adjustment to further control for any residual imbalance and to strengthen causal inference.

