### Study Geography

For this study, the government of UP has identified Shravasti and Sambhal as the intervention districts to implement the program. Keeping in view the 2-arm nature of the study, the study team has identified 2 usual care arm districts that closely match with the intervention districts using latest socio-demographic, antenatal, and immediate postpartum care indicators for the district (NFHS-5, 2019‐2021) [13]. Identified Gonda as the matching usual care arm district for Shravasti. The distance between these 2 districts is less than 50 km. Identified Budaun as matching usual care arm district to Sambhal. The distance between these 2 districts is less than 100 km. Table 1 provides sociodemographic and ANC and delivery practices in 4 study districts, and Figure 2 depicts the 4 study districts. The matched control districts were approved by the government of UP.

**Table 1. T1:** Sociodemographic and health care–seeking profile of 4 study districts.

	Intervention arm districts		Usual care arm districts	
	Shravasti	Sambhal	Gonda	Budaun
Sociodemographic profile^a^				
Population (2011), n	1,117,361	2,199,774	3,433,919	3,681,896
Sex ratio of population, (females per 1000 males)	881	891	921	871
Urban population, %^b^	4	3	7	22
Tahsils, n	3	3	4	6
Villages, n	541	993	1817	2061
Literacy, %^b^	47	55	59	53
Scheduled caste population, %^b^	16.9	16.6	15.5	17.7
ANC^c^, delivery, and immediate postpartum care indicators (2019‐2021)^d^, %^e^				
Received at least 4 ANC visits	42.3	32.9	41.7	40.6
Mothers protected against tetanus toxoid	94.4	90.3	90.4	90.1
Mothers who consumed 100 iron-folic acid	16.6	21.3	17.2	15.9
Institutional births	80.4	74.2	81.8	72.3
Mothers who received postnatal care in 2 days	68.3	67.5	68.6	62.4
Mothers received MCP^f^ card	95.9	93.5	97.1	94.4

a Master data: Census 2011-state and district wise primary census abstract.

b These are census percentages.

c ANC: antenatal care.

d International Institute for Population Sciences (IIPS) and ICF. 2021. National Family Health Survey-5, India, 2019‐21: Uttar Pradesh. Mumbai: IIPS.

e Weighted percentages.

f MCP: Mother and Child Protection.

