We will use the DiD technique to estimate the causal effect of program interventions on outputs (eg, RDW sensitized and HRPs diagnosed early) and outcomes (eg, protocol-based management and referral of HRPs). This approach compares changes in outputs and outcomes over the intervention period (18 months) between the intervention and the usual care arms. For each quantitative output and outcome indicator summary, descriptive DiD or net change will provide causal effect of intervention on the indicator. The DiD-specific regression models will then be used to test whether interventions were significantly associated with changes in the outcomes and to assess the extent of changes relative to the control group.

To address the issue of missing data in the RDW dataset, before applying DiD, we will assess the extent and patterns of missingness—whether missing data are at baseline, end line, or both—and examine whether missingness is random or systematically related to intervention status or outcomes by comparing covariates and outcomes between complete and missing cases. Given the robust data quality assurance measures implemented during both surveys, we anticipate minimal missingness, and any missing data are expected to be missing at random. If the proportion of missing at random for any outcome or covariate exceeds 10%, we will apply appropriate imputation methods prior to fitting the DiD model. The DiD model will then include intervention and control status, baseline and end line survey indicators, and interaction terms between outcomes and covariates.

During the granular analysis of testing the association between background characteristics and output and outcome indicators, we will draw upon the WHO’s Social Determinants of Health framework [45]. Intersectionality between the background and confounding variables will be explored using subgroup analysis. In the multivariate regression model, predictor variables will only be included after testing for multicollinearity using variance inflation factor to ensure stability and reliability of the model.

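### A pooled comparison of two against two non-randomly chosen districts is said to give a causal effect and generalizable evidence; the stated DiD model names no pair term, and urban residence is not a named covariate

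*Protocol article*

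**What the plan says.** Study Design describes a "matched, before-after quasi-experimental design with a control (usual care) arm". Under Study Geography, "the government of UP has identified Shravasti and Sambhal as the intervention districts", and the study team then chose a control for each: "Identified Gonda as the matching usual care arm district for Shravasti" and "Identified Budaun as matching usual care arm district to Sambhal".

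The plan for handling baseline differences, also in Study Design, is "near-matching of intervention and control data on key covariates, such as age, parity, caste, and literacy", followed by covariate-adjusted DiD. Covariates are to be prespecified when the analysis plan is locked. Data Analysis lists the DiD model terms as arm, survey round, and interactions between outcomes and covariates. No pair or district term is named there, and the outcomes with a stated contrast under Hypothesis and Outcomes compare intervention with control arm. The background items in Table 3 do not include urban or rural residence.

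On interpretation, Data Analysis says that "descriptive DiD or net change will provide causal effect of intervention on the indicator". The Overview under Rationale for the Study says that "the UP impact evaluation design is expected to provide generalizable evidence". The limitations in the Discussion cover permissions, staff turnover, transfers and social desirability. They mention neither the number of districts nor parallel trends.

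**The concern.** The programme is delivered district-wide, so the district is the unit that receives it. There are two such units per arm, and they were not randomized. The surveys measure each district once before and once after, and no midline is planned. Anything that changes in one district over that period (staffing, supply, another scheme, a private-sector shift) enters the net change exactly as a programme effect would. More women per district do not help.

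A descriptive net change therefore gives the programme effect only if the districts would otherwise have moved in parallel. The article does not state that assumption, and one pre-intervention survey cannot test it. The results are meant to inform scale-up to all 75 districts, so the wording matters.

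The pairs are the one feature of the design that could show whether a result repeats. A pooled contrast reported alone could rest on one pair without the reader seeing it.

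**Working it through.** **1. The plan's own figure.** The sample size is a one-proportion precision figure: n = 1.96² × 0.05 × 0.95 / 0.01², about 1825, as stated and then rounded to 2000 per arm per round. It contains no DiD contrast and no between-district variation, so it says nothing about the claim at issue.

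**2. How alike the pairs are (Table 1).** The urban row reads "Urban population, %^b^ 4 3 7 22", in the order Shravasti, Sambhal, Gonda, Budaun.

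| Indicator, % | Shravasti v Gonda | Gap, points | Sambhal v Budaun | Gap, points |
|---|---|---|---|---|
| Urban | 4 v 7 | 3 | 3 v 22 | 19 |
| Literacy | 47 v 59 | 12 | 55 v 53 | 2 |
| At least 4 ANC visits | 42.3 v 41.7 | 0.6 | 32.9 v 40.6 | 7.7 |
| 100 iron-folic acid | 16.6 v 17.2 | 0.6 | 21.3 v 15.9 | 5.4 |

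The pairs differ on different variables. The 19-point urban gap is the largest percentage-point gap within a pair in the table.

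**3. What the urban gap could do.** DiD removes fixed level differences, so bias arises only if urban and rural trends differ. Bias = gap in urban share × difference in trend. Assume that the sample mirrors the 2011 census shares and that the districts count equally. The arms are then (4 + 3)/2 = 3.5% and (7 + 22)/2 = 14.5% urban, a gap of 11 points.

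| Assumed urban-rural trend difference, points | Bias in Sambhal-Budaun, points | Bias in pooled DiD, points |
|---|---|---|
| 5 | 0.19 × 5 = 0.95 | 0.11 × 5 = 0.55 |
| 10 | 1.9 | 1.1 |
| 20 | 3.8 | 2.2 |

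**4. What district-specific change could do.** Let district changes vary with SD τ. With two districts per arm, they add variance τ²(1/2 + 1/2) = τ² to the DiD. A test that uses only the within-survey standard error s has true type I error 2 × [1 − Φ(1.96 s / √(s² + τ²))].

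Take s = 3.8 points. With an outcome proportion of 50% and no clustering, s = √(4 × 0.25 / n), so this corresponds to about 690 affected women per arm per round. The condition-specific counts in the sample size section sum to between 400 + 120 + 100 = 620 and 500 + 200 + 340 = 1040, ignoring overlap, which gives s = 4.0 to 3.1.

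- τ = 3: 1.96 × 3.8 / √(14.44 + 9) = 1.54, type I error 12.4%.
- τ = 5: 1.96 × 3.8 / √(14.44 + 25) = 1.19, type I error 23.6%.

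Over n = 620 to 1040, the error is 8-10% at τ = 2, 12-16% at τ = 3 and 22-30% at τ = 5.

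**5. Inference with the district as the unit.** Four units allow 6 unpaired or 4 paired allocations. The smallest two-sided permutation p-value is 2/6 = 0.33 unpaired and 2/4 = 0.50 paired. The t critical value is 4.30 (2 df) or 12.71 (1 df), against 1.96 for individuals.

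**6. What pair terms would change.** With about 1000 women planned per district, the pooled linear DiD is close to the average of the two pair-specific DiDs. Pair terms therefore barely move the estimate. Their use is to show both components, each with a confidence interval about √2 = 1.4 times wider.

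**The case against.** A reader might infer that the pairs are discarded and that urban residence is excluded. The article does not say so. It names no pair term in a one-sentence model summary, its covariate list is given as examples, and the list is still to be locked. The full plan may contain both items.

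A reader might also infer that 22% against 3% biases the result. It does not by itself: trends must differ by residence, and the pooled bias in the range shown is modest. Nor is the urban share of the sample known. Sampling units are ASHA (accredited social health activist) areas, which the article places at village level, so the sampled gap may be much smaller than the census gap.

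A third tempting step is to accept benefit only if both pairs point the same way. Under no effect, two independent pairs are both positive one time in four, so this is a weak safeguard, and it costs power. It is not recommended here.

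The article is also partly cautious. It acknowledges nonrandom allocation, calls the Uttar Pradesh work a pilot meant to give early evidence, and describes the regression step in terms of association.

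All of this stands. It does not remove the two unqualified statements: a descriptive net change is equated with a causal effect, and two intervention districts are expected to yield generalizable evidence. Neither is qualified in the limitations.

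**Conclusion.** The point holds as one of overclaiming, together with an analysis description that does not use the matched pairs. The design cannot separate the programme from district-specific change, and the planned surveys cannot check parallel trends. If district changes have an SD of 3 to 5 points and the within-survey standard error is 3.8 points, a nominal 5% individual-level test errs about 12% to 24% of the time. Both inputs are assumptions. Clustering within sampling units, ignored in deriving the standard error, would raise it and reduce this relative inflation.

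The urban gap is secondary: about 1.1 points of pooled bias under an assumed 10-point trend difference and census shares from 2011. Neither pair terms nor residence adjustment repairs inference from four districts. They make the limit visible.

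**What to change.** 1. In the locked plan, include pair and pair-by-period terms beside the arm-by-period term that defines the DiD. Report both pair-specific DiDs with confidence intervals beside the pooled one.
2. Add urban or rural residence of the sampling unit as an adjustment covariate where it can be derived from the unit's location. The article does not list it as recorded, so this needs checking. Any use of 3.5% against 14.5% as sample urban shares should be labelled an assumption from the 2011 census.
3. In Data Analysis, say that the DiD estimates the programme effect in these districts under a parallel-trends assumption that the planned surveys cannot test. Qualify the generalizability sentence in the Overview under Rationale for the Study in the same way.
4. Add to the limitations in the Discussion that there are two districts per arm, chosen without randomization, with one survey before and one after.

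The cost is wording plus two extra estimates per outcome. The pair-specific intervals will be about 1.4 times wider than the pooled one. No new sample is needed, and no new data if residence can be derived from location.

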### Duration of Interventions and Justification for Creating a Usual Care Arm

In 2 intervention districts, the IHRPTM program will be implemented district-wide for 18 months, starting June-July 2024 and ending February-March 2026. The 18-month duration is necessary, as the introduction of different interventions in both the intervention districts requires 3‐6-month time. Also, for converting system level changes into outcomes is a time-consuming process [35]. Given the relatively short implementation period, we are not proposing a midline evaluation. However, the uptake, quality, and coverage of interventions will be continuously monitored through a robust monitoring system. Dipstick studies will be conducted depending upon the need. Any mid-course corrections will be based on findings from the baseline, monitoring data, and dipstick studies.

In the usual care arm, HWs will receive routine capacity-building sessions conducted by the state and the national governments. Pregnant women in both arms will have access to antepartum, intrapartum, and postpartum care programs provided by the state and the national governments. It implies that while general system strengthening interventions are provided in both the arms, the IHRPTM interventions are the only additional interventions confined to the intervention arm. At the community level, the IHRPTM program does not directly work with pregnant women in either arm. The control arm was included to isolate the effect of the IHRPTM interventions from the general system strengthening activities and to assess whether IHRPTM interventions had any incremental effect or value addition beyond what general system strengthening interventions alone can achieve. Thus, this study design ensures ethical equity while also allowing us to isolate the incremental effect of the IHRPTM program interventions by comparing changes in outcomes that go beyond improvements expected from broader system strengthening efforts.

### Study Geography

For this study, the government of UP has identified Shravasti and Sambhal as the intervention districts to implement the program. Keeping in view the 2-arm nature of the study, the study team has identified 2 usual care arm districts that closely match with the intervention districts using latest socio-demographic, antenatal, and immediate postpartum care indicators for the district (NFHS-5, 2019‐2021) [13]. Identified Gonda as the matching usual care arm district for Shravasti. The distance between these 2 districts is less than 50 km. Identified Budaun as matching usual care arm district to Sambhal. The distance between these 2 districts is less than 100 km. Table 1 provides sociodemographic and ANC and delivery practices in 4 study districts, and Figure 2 depicts the 4 study districts. The matched control districts were approved by the government of UP.

**Table 1. T1:** Sociodemographic and health care–seeking profile of 4 study districts.

	Intervention arm districts		Usual care arm districts	
	Shravasti	Sambhal	Gonda	Budaun
Sociodemographic profile^a^				
Population (2011), n	1,117,361	2,199,774	3,433,919	3,681,896
Sex ratio of population, (females per 1000 males)	881	891	921	871
Urban population, %^b^	4	3	7	22
Tahsils, n	3	3	4	6
Villages, n	541	993	1817	2061
Literacy, %^b^	47	55	59	53
Scheduled caste population, %^b^	16.9	16.6	15.5	17.7
ANC^c^, delivery, and immediate postpartum care indicators (2019‐2021)^d^, %^e^				
Received at least 4 ANC visits	42.3	32.9	41.7	40.6
Mothers protected against tetanus toxoid	94.4	90.3	90.4	90.1
Mothers who consumed 100 iron-folic acid	16.6	21.3	17.2	15.9
Institutional births	80.4	74.2	81.8	72.3
Mothers who received postnatal care in 2 days	68.3	67.5	68.6	62.4
Mothers received MCP^f^ card	95.9	93.5	97.1	94.4

a Master data: Census 2011-state and district wise primary census abstract.

b These are census percentages.

c ANC: antenatal care.

d International Institute for Population Sciences (IIPS) and ICF. 2021. National Family Health Survey-5, India, 2019‐21: Uttar Pradesh. Mumbai: IIPS.

e Weighted percentages.

f MCP: Mother and Child Protection.

**Figure 2. F2:**
[figure not shown]
Intervention and control districts of Uttar Pradesh (adapted from OpenStreetMap data [36] using DataWrapper software [37], and published under Creative Commons Attribution-ShareAlike 2.0 Generic License [38]).

### Study Tools

Baseline and end line surveys will use qualitative methods for collecting data from the system stakeholders and quantitative methods for collecting data from the community, specifically the RDW. The data collection tools were pretested in Telangana in 2022-2023 and subsequently adapted to align with the programs and policies of UP. Table 2 provides details of respondents interviewed using qualitative data collection technique.

**Table 2. T2:** Respondents, data collection method, sample size, and information areas of qualitative data collection tools.

Type of respondent and tool	Data collection method	Sample size	Who collects data?	Recruitment strategy	Key information areas of tool
Chief medical officer (Multimedia Appendix 1)	In-depth interview	1 per district	Qualitative researchers	Purposive	District policies and programs on maternal and newborn health Facilitators and barriers to implement IHRPTM^a^ program in district
Associate chief medical officer (Multimedia Appendix 2)	Semistructured interview	1 per district	Qualitative researchers	Purposive	Most prevalent HRPs^b^ in district Vulnerable areas or populations Issues with collection of RCH^c^, HMIS^d^, or HRP data Human resources availability
Specialist gynecologists (district hospital; Multimedia Appendix 3)	In-depth interview	1 per district	Qualitative researchers	Purposive	ANC^e^ case load at facility HRP case load at facility Volume of high-risk cases referred to facility Volume of late and unnecessary referrals Strategies for coping with referrals
Medical officers working in PHC^f^ and CHC^g^ (Multimedia Appendix 4)	Semistructured interview	4‐5 per district	Qualitative researchers	From 4 randomly selected PHCs of 2 blocks in a district	Support systems available for ensuring quality ANC Case load of ANC and HRPs Knowledge about 3 specific HRPs Management skills to care for women with 3 HRPs Knowledge about referral practices to woman with 3 HRPs
ANMs^h^ working in HSCs^i^ (Multimedia Appendix 5)	Semistructured interview	8‐10 per district	Qualitative researchers	2 ANMs per PHC, from above 4 randomly selected PHCs of 2 blocks in a district	Support systems available for ensuring quality ANC Case load of ANC and HRPs Knowledge about 3 specific HRPs Management skills to care woman with 3 HRPs Knowledge about referral practices to woman with 3 HRPs

a IHRPTM: Integrated High-Risk Pregnancy Tracking and Management.

b HRP: high-risk pregnancy.

c RCH: reproductive and child health.

d HMIS: health management information system.

e ANC: antenatal care.

f PHC: primary health center.

g CHC: community health center.

h ANM: auxiliary nurse midwives.

i HSC: health subcenter.

### Community-Level Data Collection

RDW who gave birth within the past year, regardless of HRP status, will be surveyed in all the 4 study districts, at baseline and at end line. Some unique features of the RDW tool are documentation of the previous pregnancy, including details of HRP condition (if applicable), as a story in mother’s own words; a picture of the Mother and Child Protection card to supplement with the question-specific data collected from the RDW through interview; ANC details; and HRP-specific detailed questions, where applicable (Table 3; Multimedia Appendix 6).

**Table 3. T3:** Key data collected in the recently delivered women tool.

Data point collected	Details
Pregnancy and delivery details	Age, delivery date, type and place of delivery, outcome of delivery, child’s age, birth weight, term and preterm status, MCP^a^ card availability, and HRP^b^ status
Reproductive history	Children ever born and surviving, and pregnancy terminations
MCP card photo	With details of each ANC^c^ visit, in picture format
Story of recent pregnancy in mother’s own words	Investigators ask the mother to describe about her most recent pregnancy in her own words, from conception to delivery, including details of any HRP, if applicable. The story told by mother is documented here in a text format
ANC characteristics	Number of ANC visits, details of first ANC visit, experience of risk factors, TT^d^ and IFA^e^ usage, supplementary nutrition, and high-risk conditions experienced, including duration of problem and referrals made for the HRP
Delivery and newborn characteristics	Breech presentation, prolonged labor, excessive bleeding, facility stay after delivery, congenital anomalies, and reasons for cesarean section
Details about severe or moderate anemia, PIH^f^, APH^g^, and other HRP conditions experienced by mother in most recent pregnancy (if applicable)	Timing of first diagnosis of HRP and who diagnosed, risk factors associated with the HRP, and management, referral, counseling, and follow-up details related to the HRP condition
Satisfaction	Level of satisfaction with care received if HRP was present
Background characteristics	Literacy, schooling, religion, caste or tribe, occupation, and owning of own mobile phone by the mother

a MCP: Mother and Child Protection.

b HRP: high-risk pregnancy.

c ANC: antenatal care.

d TT: tetanus toxoid.

e IFA: iron-folic acid.

f PIH: pregnancy-induced hypertension.

g APH: antepartum hemorrhage.

